### 9.3.2.2 Secondary endpoints analyses

These will also be analysed using GLMs with the treatment arm as the single predictor and country (Kenya, Malawi and Tanzania) and gravidity (pauci and multigravidae) as control variables. The point estimate of the treatment effects with 95% CI will be derived via specification of a GLM model for each secondary outcome depending on its distribution. For a binary outcome such as the components of primary endpoint, similar analysis to the primary endpoint analysis will be performed and the treatment effects measured as RR will be generated. For a continuous outcome like birthweight, a Gaussian distribution will be assumed and identity link function will be used. Correspondingly the mean difference and its 95%CI between two arms will be calculated. For a count outcome such as the number of SAEs, Poisson distribution and log link function will be used, from which incidence rate ratio (IRR) and its 95% CI will be computed.

### 9.3.2.3 Subgroup analyses

We will perform subgroup analyses of the primary endpoint and its components on the following baseline characteristics of women: study site, gravidity (1st, 2nd 3rd and 4th+), malaria status (positive-negative, based on a composite of microscopy and PCR), socio-economic status (terciles), season (terciles of average rainfall last 6 months before delivery), and site characteristics: malaria transmission intensity, expressed as prevalence of PCR positivity on enrolment across 3 arms; and degree of SP parasite resistance, expressed as prevalence of the 'quintuple' and 'sextuple' *dhfr/dhps* mutant parasites or other variations of resistance markers. We will also conduct subgroup analysis for the effect of the number of courses received (e.g. <4 vs 4+). The treatment effect within each category of the above selected variables will be estimated and the interaction effect between treatment and each variable assessed to explore effect modification. The modifying effects of bednets cannot be assessed as all women will receive LLINs on enrolment as part of the national policy.

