## 7.2 ELIGIBILITY CRITERIA

### 7.2.1 Inclusion criteria

Pregnant women between 16-28 (both inclusive) weeks gestation, who have a viable singleton pregnancy, resident of the study area, willing to adhere to scheduled and unscheduled study visit procedures, and willing to deliver in a study clinic or hospital.

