## 7.4 OUTCOMES

### 7.4.1 Primary outcome

#### Adverse pregnancy outcome

The primary outcome is 'Adverse pregnancy outcome' defined as the composite of foetal loss (spontaneous abortion or stillbirth), or singleton live births born small-for-gestational age (SGA), or with low birthweight (LBW), or preterm (PT) (SGA-LBW-PT), or subsequent neonatal death by day 28. Small for gestational age will be defined using the new INTERGROWTH population reference's 10th percentile.

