### 7.7.2 Planned recruitment rate

Recruitment of 4,680 women (all gravidae) from 10 sites will require 17 months, with an additional 7 months to complete pregnancy plus infant follow-up. The recruitment rate of 280 HIV-negative women per month, or an average of 28 per site was the average recruitment in the most recent malaria in pregnancy interventions trials in Malawi and Kenya, conducted by the same teams. This corresponds to approximately 1 delivery per day per site, which is an adequate workload that helps ensure the teams are not overburdened and the data quality and completeness of follow-up is maintained to the highest standards.

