### 9.1 PROCEDURES FOR ASSESSING EFFICACY AND SAFETY PARAMETERS

#### 9.1.1 Efficacy

##### 9.1.1.1 SGA-LBW-PT

New-borns will be weighed within 24 hours of delivery using digital scales ( $\pm 10$  gr) and LBW defined as  $< 2,500$ g. Gestational age will be assessed using ultrasound dating at enrolment and preterm (PT) defined as  $< 37$  weeks' gestation. Small for gestational age (SGA) will be defined as birthweight below the tenth percentile for a given gestational age and sex, using the new INTERGROWTH reference population. This will also allow the calculation of Z-scores.

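### Season is listed as a baseline subgroup but is dated from delivery, so membership depends on the preterm and foetal-loss outcomes and a treatment-by-season interaction can be distorted

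*Protocol*

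**What the plan says.** Section 9.3.2.3 of the protocol opens its list with "We will perform subgroup analyses of the primary endpoint and its components on the following baseline characteristics of women". Season is on that list, defined as "season (terciles of average rainfall last 6 months before delivery". The stated aim is to estimate the treatment effect within each category, with "the interaction effect between treatment and each variable assessed to explore effect modification". The number of courses received, which is clearly post-randomisation, is named in a separate sentence outside the baseline list.

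The primary outcome (section 7.4.1) combines foetal loss with live births that are small for gestational age, of low birthweight, "or preterm (PT) (SGA-LBW-PT), or subsequent neonatal death by day 28". Women enter at 16 to 28 weeks (section 7.2.1). Section 9.1.1.1 states: "Gestational age will be assessed using ultrasound dating at enrolment". An expected delivery date is therefore known for every woman at randomisation.

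**The concern.** A subgroup variable should be fixed before treatment starts, or at least be unaffected by the outcome under study. This one is neither. For preterm birth and foetal loss, the event itself sets the date from which rainfall is counted back. Two women with the same enrolment date and the same due date can land in different rainfall terciles only because one delivered early or lost the pregnancy. Section 9.3.2.3 also applies the subgroups to the components of the endpoint, so preterm birth and foetal loss are each to be analysed by a variable that they help to determine.

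At stake is the reading of the season interaction. If events are sorted into terciles differently from non-events, a real interaction can be understated, and a null result is then hard to interpret.

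**Working it through.** **1. The plan's own figures.** The protocol states no figure for the season subgroup. Its main sample size (section 7.6.1.2) reproduces. With p1 = 0.213, p2 = 0.80 × 0.213 = 0.1704 and mean p = 0.1917:

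n = [1.960 × √(2 × 0.1917 × 0.8083) + 0.842 × √(0.213 × 0.787 + 0.1704 × 0.8296)]² / 0.0426² = (1.0911 + 0.4678)² / 0.001815 ≈ 1,340 per arm, as stated.

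One tercile holds about 1,345 / 3 ≈ 448 women per arm. Its power for a risk ratio (RR) of 0.80 is Φ[(0.0426 × √448 − 1.0911) / 0.5559] = Φ(−0.34) ≈ 37%.

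**2. What the window covers** (6 months taken as 26 weeks).

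- Birth at 40 weeks: gestational weeks 14 to 40, roughly the intervention period.
- Birth 5 weeks early, at 35 weeks: weeks 9 to 35.
- Loss at 20 weeks in a woman enrolled at 16: weeks −6 to 20. Of the 26 weeks, 22 precede randomisation and 6 precede the start of gestational dating.

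**3. Size of the effect, by simulation** (3 million women per scenario). From the protocol: a 21.3% control risk, entry at 16-28 weeks and 17 months of recruitment (section 7.7.2; section 7.7.3 says 18). Assumed, because the protocol does not give them: smooth rainfall curves with one or two peaks a year; 25-60% of events preterm and 20-22% losses; preterm births on average about 5 weeks before the due date; losses 0-150 days before it.

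*Reclassification.* 45-51% of preterm births and losses change tercile relative to the due-date window, against about 8% of other women. A second set of assumptions (year-round enrolment, preterm births 3-9 weeks early, losses 4-20 weeks early) gives 53-56% against 10%.

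*Recovery of a true interaction* with RRs 1.0/0.8/0.6 from lowest to highest rainfall (one peak, 40% preterm, 20% losses):

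| True modifier | Due-date window | High/low ratio | Actual-delivery window (protocol) | High/low ratio |
|---|---|---|---|---|
| Season by expected delivery date | 1.01/0.80/0.60 | 0.60 | 0.95/0.81/0.66 | 0.70 |
| Rainfall before actual delivery | 0.93/0.80/0.64 | 0.69 | 0.98/0.80/0.61 | 0.62 |

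In the first row the log contrast shrinks by 1 − ln(0.698)/ln(0.60) = 1 − 0.360/0.511 ≈ 30%. The high/low ratio stayed at 0.68-0.72 across the assumed preterm shares, one or two rainfall peaks, and 12, 17 or 24 months of recruitment.

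*Foetal loss alone.* Under the second set of assumptions, true RRs of 0.95/0.80/0.60 appear as about 0.90/0.80/0.65 for the composite. For foetal loss they appear as about 0.79/0.78/0.75, so the interaction almost disappears.

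*No true interaction.* With no seasonal modification of the treatment effect, the high/low ratio was 0.995-1.03. A flat control risk of 21.3% appeared as about 20% to 23% across terciles with 17 months of enrolment, but not when enrolment covered whole calendar years.

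**The case against.** The strongest objection is that the size of the dilution presupposes which window is the true modifier. The protocol does not say. If rainfall actually experienced before delivery is what matters, the protocol's window recovers 0.62 against a true 0.60, while the due-date window gives 0.69. For early losses the due-date window also has an evident flaw. With a loss at 20 weeks, about 20 of its 26 weeks (weeks 20 to 40) fall after the pregnancy has ended. Both points stand, so the direction of distortion must be left open. Neither makes a delivery-dated variable baseline or independent of the outcome.

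The consequence is also small. The analysis is exploratory, power within a tercile is already low, and season is one of several listed modifiers beside gravidity and malaria status at entry. This stands too, and it sets the severity.

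A reader might infer that early births and losses are all moved to another season. The check does not support that: about half keep their tercile, because a shift of a few weeks leaves most of a six-month window unchanged. A reader might also infer that the protocol's definition would manufacture a season interaction. It produces almost none when the RR is constant.

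**Conclusion.** The point holds, at low severity. Season as defined in section 9.3.2.3 is not a baseline characteristic, and for two components of the endpoint the outcome itself sets subgroup membership. That follows from the text alone and needs no assumption.

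The size does rest on assumptions about rainfall, event mix and timing that the protocol does not supply. Under them, roughly half of preterm births and losses change tercile, against about 8-10% of other women. An interaction is probably diluted, by about 30% on the log scale, if the modifier is season by expected delivery date. This does not hold if the modifier is rainfall before actual delivery. It would go too far to say that a real seasonal effect is certainly diluted, or that the treatment comparison is invalid. The primary analysis and the sample size do not use this variable and are unaffected.

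**What to change.** In section 9.3.2.3, define season as terciles of average rainfall over the 6 months before the expected delivery date, taken from the enrolment ultrasound. Keep the actual-delivery window only as a sensitivity analysis, labelled as not baseline. Rainfall before enrolment is not an equivalent substitute: in the simulation it captured a different season and the high/low ratio reversed to about 1.25.

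The cost is one line, settled before unblinding. No new data are needed from the women, and the same kind of rainfall series serves both windows. The small price is that for early losses the due-date window includes weeks after the pregnancy ended, which the sensitivity analysis helps to judge.

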### 9.3.3 Safety

For the safety analysis, women in the IPTp-DP arm will be considered overall and by number of DP courses, alone and combined with AZ, received to explore dose-responses using GLM.

### 9.3.4 Meta-analysis

Subject to the timely availability of individual datasets, a prospective individual participant data (IPD) meta-analysis is planned following the completion of this trial using data from all available trials comparing IPTp-DP with IPTp-SP in Africa. This is currently estimated to involve a total of 4 or 5 trials, including this proposed trial, the 2 completed trials, and 2 other smaller planned trials in Uganda and Malawi (see section 4.2, Other relevant research ongoing elsewhere, page 21). The statistics for each trial will be combined to estimate the pooled effect size and associated confidence intervals for the meta-analyses. The analysis will follow the new PRISMA-IPD statement guidelines. All PIs have agreed to share their existing and prospective data bases for this purpose.

## 10 METHODS: MONITORING

---

### 10.1 DATA MONITORING AND TRIAL OVERSIGHT COMMITTEES

#### 10.1.1 Data Monitoring and Ethics Committee (DMEC)

Since the study is a clinical trial an independent Data Monitoring and Ethics Committee (DMEC) will be set up. The DMEC will be critical to ensure that the subjects are protected from harm, while also

ensuring that the study integrity is not compromised. The DMEC will consist of 3 to 4 independent members knowledgeable in the conduct of clinical trials. They will meet regularly (e.g. twice yearly or more frequent if so required) during data collection period to provide a review of blinded (and if requested unblinded) data to ensure the safety, rights and well-being of trial participants. In addition, regular review of the quality of the study data will be conducted at each meeting of the DMEC.

The roles and membership of the DMEC are described in more detail in Appendix II. Terms of reference oversight committees, section 16.2, page 71.

#### 10.1.2 Trial Steering Committee (TSC)

The trial will also have a Trial Steering Committee (TSC) which will advise on the study amendments, monitor progress and quality of the trial, ensure women's rights and safety are adhered to, review relevant new information from other sources and consider recommendations from the DMEC. The role and membership of the TSC are also described in more detail in Appendix II. Terms of reference oversight committees, section 16.2, page 71.

#### 10.1.3 Interim sample size re-estimation and/or interim analyses and criteria for termination of the trial

##### 10.1.3.1 Sample size re-estimation

One interim sample size-estimation will be conducted when approximately 50% of women have been recruited to verify if the trial is not under-powered based on potential differences between the observed event and dropout rate pooled across the three arms (i.e. blinded) and the estimates of these pooled rates used in the sample size calculations, which were based on historical data from the study areas. To maintain Type 1 error and trial integrity and safeguard the power of the trial, this will be conducted blinded; i.e. the effect size will not be taken into consideration as no details by arm will be provided to the statistician conducting the sample size re-estimation

##### 10.1.3.2 Interim analysis

An interim analysis will be conducted on the primary endpoint when approximately 75% of participants have enrolled or at a time point suggested by the TSC or DSMB. The interim-analysis will be performed by an independent statistician, blinded for the treatment allocation. The statistician will report to the independent DMEC. The DMEC will have unblinded access to all data and will discuss or report the results of the interim-analysis with the Trial Steering Committee (TSC), e.g. in a joint meeting. The TSC decides on the continuation of the trial and will report to the ethics committees.

The Lan-DeMets spending function with O'Brien-Fleming type boundaries will be employed and the sample size inflated (see 7.6.1.2, page 37) to preserve the overall one-sided type I error rate for efficacy at the  $\alpha=0.05$  level at the final analysis. If the stopping boundary is crossed at the interim analysis and the RR is less than 1, i.e. the observed prevalence of the primary endpoint in the intervention arm is less than the expected prevalence under the null hypothesis, it will be concluded that the study has demonstrated that the efficacy of the intervention is superior to that of IPTp-SP in the prevention of the primary outcome. The trial recruitment can then be stopped unless the DMEC advises otherwise. Statistics will not be the sole basis for the decision to stop or continue and the DMEC can advise to continue recruiting in the trial (e.g. in 2 of the 3 arms), or stop recruiting but continue to complete the intervention as per randomization in the remaining active women, even if statistically the stopping boundary is crossed, e.g. in order to continue collecting more safety

information or data for further sub-group analyses etc. The trial will not be stopped in case of futility, unless the DMEC during the course of safety monitoring advises otherwise.

A detailed plan for interim analysis, the provisional stopping rules and how the stopping rules will be applied, will be drawn up prior to the start of the interim analysis and documented in the study statistical analysis plan.

In addition, regular review of the quality of the study data will be conducted at each meeting of the DMEC.

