#### 16.2.2.4 Frequency of Meetings

The TSC shall have an initial face to face start up meeting to discuss the protocol and establish the DMEC. A second meeting shall take place before the initiation of the trial to finalise the protocol and approve the commencement of the trial. Thereafter the TSC will normally meet once a year in the life span of the trial and one meeting at the closure of the trial.

The Chair and at least 2 of the three independent members together with the CI and trial co-ordinator shall constitute the quorum. If so required, in addition a member of the funder can be invited to attend the meetings.

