### 16.2.3.2 Role DMEC

The DMEC consist of 3-4 members (including one or more clinicians and one statistician, all with experience in clinical trials).

The DMEC shall assess the data regularly (before the annual TSC meeting) to review the data and the interim analysis. The assessment could be via email or other electronic medium annually prior to the TSC meeting. In the first year of recruitment more frequent assessment (bi-annually) is recommended for this trial with one face to face meeting at least once during the trial.

The members should be the only personnel to see the results separated by treatment group during the trial. They are independent and look at the trial from an ethical point of view of the participant safety, future participants and society in general. It is their responsibility to prevent participants being exposed to any excess risks by recommending to the Trial Steering Committee (TSC) for the trial suspension or termination early if the safety or efficacy results are sufficiently convincing. The trial statistician is usually invited to attend part of the DMEC meeting to present the most current data from the trial. This will be blinded, unless the DMEC specifically requests for an unblinded analysis.

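### The interim section has the DMEC share results with a steering committee whose quorum includes the chief investigator and trial co-ordinator, while Appendix II keeps results by arm within the DMEC

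*Protocol*

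**What the plan says.** Protocol 10.1.3.2 sets the timing and content of the look: "An interim analysis will be conducted on the primary endpoint when approximately 75% of participants have enrolled". The criterion is a comparison with IPTp-SP: "If the stopping boundary is crossed at the interim analysis and the RR is less than 1", superiority is concluded. The work is done by a statistician outside the trial: "The interim-analysis will be performed by an independent statistician, blinded for the treatment allocation". That statistician reports to the DMEC, whose members may look at everything unblinded. The section then states that this committee "will discuss or report the results of the interim-analysis with the Trial Steering Committee (TSC), e.g. in a joint meeting". Whether the trial goes on is left to the steering committee.

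On who sits at a TSC meeting, 16.2.2.4 says: "The Chair and at least 2 of the three independent members together with the CI and trial co-ordinator shall constitute the quorum". On who may see comparative data, 16.2.3.2 says of the DMEC: "The members should be the only personnel to see the results separated by treatment group during the trial".

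The protocol describes the flow from DMEC to TSC in two ways. Sections 10.1.2, 16.2.2.2 and 16.2.3.3 describe a recommendation: the TSC considers what the DMEC advises, and the DMEC advises to continue, modify or stop. Section 16.2.3.3 also treats release of interim data as something to be requested and weighed. Sections 10.1.3.2 and 16.2.2.3, in contrast, speak of discussing or reporting the results of the interim analysis.

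Section 16.2.3.2 adds that the trial statistician is usually invited to part of the DMEC meeting to present current data, and continues: "This will be blinded, unless the DMEC specifically requests for an unblinded analysis".

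**The concern.** Two rules on access to interim results cannot both be followed. Under one, the steering committee hears the results, and it cannot be quorate without the two people who lead and co-ordinate the trial. Under the other, nobody outside the DMEC sees results by treatment group while the trial runs.

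The look does not end data collection. The protocol has no futility stop, and the DMEC may advise further recruitment even after the boundary is crossed, for instance in two of the three arms. Only azithromycin has a placebo. SP is a one-day course and DP a three-day course, so site staff and participants can tell DP from SP. If the trial's leaders know the interim effect in that setting, it can affect the effort put into recruiting, into keeping women in follow-up and into running the arms. Data gathered after the look are then no longer independent of the result at the look, and no analysis can repair that afterwards.

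**Working it through.** The access rule itself involves no arithmetic, so the passages are set side by side first. The exposure after the look is then sized.

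**Access rule**

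1. The interim analysis applies a stopping boundary to the risk ratio for the primary endpoint against IPTp-SP (10.1.3.2). Its results are therefore a between-arm comparison.
2. Those results are to be discussed with, or reported to, the TSC (10.1.3.2). Section 16.2.2.3 also has the DMEC report interim results.
3. A quorate TSC meeting includes the chief investigator and the trial co-ordinator (16.2.2.4). No section provides a closed session without them.
4. Results separated by treatment group are for DMEC members only during the trial (16.2.3.2).
5. Steps 1 to 3 put results by arm before people whom step 4 excludes. Coded arms do not resolve this: step 4 covers any separation by group, and a look at a partly masked three-arm trial may be easy to decode.
6. The information can travel further. TSC findings go to the funder, the sponsor and the Trial Management Group (16.2.2.5), and the chief investigator sits ad hoc on that group (16.2.1.2).

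**Women still to enrol at the look**

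(1 − 0.75) × 4,680 = 1,170.

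**Primary outcomes still to be collected**

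Inputs from the protocol: 17 months' recruitment (7.7.2), antenatal booking at about 22 weeks on average (6.2.3), and neonatal death counted to day 28 (7.4.1). Assumptions: uniform accrual, delivery at 39 or 40 weeks, 30.44 days per month, no losses.

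The look falls at 0.75 × 17 = 12.75 months. With *d* the months from enrolment to outcome, the share of all outcomes complete is (12.75 − *d*)/17.

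| Outcome counted as complete at | Delivery week | *d* (months) | Complete | Still to come |
|---|---|---|---|---|
| Birth | 39 | 17 × 7 / 30.44 = 3.91 | 8.84/17 = 52% | 48% |
| Birth | 40 | 18 × 7 / 30.44 = 4.14 | 8.61/17 = 51% | 49% |
| Day 28 | 39 | (17 × 7 + 28) / 30.44 = 4.83 | 7.92/17 = 47% | 53% |
| Day 28 | 40 | (18 × 7 + 28) / 30.44 = 5.06 | 7.69/17 = 45% | 55% |

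Section 7.7.3 gives 18 months instead. The look then falls at 13.5 months, and for delivery at 39 weeks the share complete is (13.5 − 3.91)/18 = 53% at birth and (13.5 − 4.83)/18 = 48% at day 28. Roughly half remains to be collected under either figure.

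**The case against.** The strongest reply is that the protocol already has the right model and 10.1.3.2 contains one loose sentence. Sections 10.1.2, 16.2.2.2 and 16.2.3.3 describe recommendations, the TSC has an independent majority (16.2.2.2), and the joint meeting is only an example. This stands as a description of most of the text, but it does not remove the conflict. Section 10.1.3.2 is the operative section for the interim analysis. It names results and not a recommendation, and an independent majority does not take the chief investigator or the co-ordinator out of the room. The TSC membership list is not in the text at hand, so their voting status is unknown; the point rests on the quorum sentence alone.

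A reader might infer more than the documents support:

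- *That unblinded results are ordered to the TSC.* In 10.1.3.2 the word unblinded describes the DMEC's own access. The interim statistician is blinded, and coded results are possible.
- *That late choices in the statistical analysis plan could be steered.* Section 8.2.1 requires DMEC approval of that plan before the DMEC reviews any results, and 9.3.1 has it signed before unblinding. That route is closed.
- *That the trial statistician is permitted to be unblinded.* Section 16.2.3.2 does not say who produces or presents an unblinded analysis. It is ambiguous; it does not grant permission.
- *That funders will hear the results.* They are listed as observers, but 16.2.2.4 makes their attendance conditional on invitation.
- *That the outcome itself would be biased.* Gestational age comes from ultrasound at enrolment, birthweight from digital scales, and laboratory staff are masked (8.2.1, 9.1.1.1). This limits influence on ascertainment, though not on recruitment or retention.
- *That more than half of the outcomes are still to come.* This depends on whether completeness is counted at birth or at day 28, and 10.1.3.2 lets the TSC or the safety board move the look.

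**Conclusion.** The concern holds as a conflict within the protocol. Following 10.1.3.2 as written, with the quorum in 16.2.2.4, breaches the access rule in 16.2.3.2 and departs from the recommendation model in 16.2.3.3. It is not a detail left to the statistical analysis plan: 10.1.3.2 defers the stopping rules, but itself fixes who receives the results.

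The exposure is about 1,170 women still to be enrolled and roughly half of the primary outcomes (48% to 55% on 17-month accrual), given a look at 75% enrolment and the stated assumptions. The bias that could follow cannot be calculated from the document, and nothing here shows that it would occur. The plausible routes are recruitment, retention and general conduct in a trial where DP versus SP is visible. The change should be made before the interim analysis, because exposure to the results cannot be undone.

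**What to change.** Reword 10.1.3.2, and align 16.2.2.3 with it, so that the DMEC sends the TSC only a recommendation (continue, modify, or stop recruitment or an arm) without results by arm, coded or not. If the DMEC recommends stopping, results by arm may be shared in a closed session limited to the TSC's independent members. Other arrangements that keep the chief investigator and co-ordinator from comparative results would also serve.

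In 16.2.3.2, state that any unblinded analysis the DMEC requests is produced and presented by a statistician independent of the trial team, not by the trial statistician.

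The cost is wording in three sections, submitted as an amendment under 11.2.2. An independent statistician is already planned, although 10.1.3.2 and 8.2.1 describe that person as blinded, so the wording must say who holds the allocation code for an unblinded request. The one real downside is that the TSC decides on continuation with less information unless stopping is recommended.
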